### Data collection

We will collect baseline characteristics from glioma patients, including age, sex, preoperative MRI datasets (T1C, T1, T2, T2 flair), CTC count, single-cell sequencing results of CTC, WHO grade, IDH, 1p/19q, ATRX, CDKN2A/B, telomerase reverse transcriptase (TERT), epidermal growth factor receptor (EGFR), +7/−10, H3.3 G34, H3K27M.

### Outcomes

#### Primary outcomes

The molecular type of 2021 WHO-CNS classification will be the primary outcome, including IDH (mutant/wild), ATRX (retain/lost), 1p/19q (codel/intact), CDKN2A/B (retain/lost), TERT/EGRF/+7/−10 (retain/lost), H3.3 G34 (mutant/wild), H3K27M mutant.

#### Secondary outcomes

WHO II/III/IV will be the secondary outcome.

### Sample size

A sample of 400 achieves 90% power to detect a difference of 0.1000 between the area under the ROC curve (AUC) under the null hypothesis of 0.7000 and an AUC under the alternative hypothesis of 0.8000 using a two-sided z-test at a significance level of 0.05000. The data are discrete (rating scale) responses. The AUC is computed between false positive rates of 0.000 and 1.000. The ratio of the standard deviation of the responses in the negative group to the standard deviation of the responses in the positive group is 1.000.

### Liquid biopsy technique

#### Collection of peripheral blood

After receiving written informed consent, peripheral blood collections were obtained from patients under Institutional Review Board-approved protocols. All patients in the study were free of significant comorbid medical conditions or prior cancer, deemed operable, and underwent a biopsy, subtotal, or gross total, surgical resection. Peripheral blood samples (5 mL × 2) were collected in EDTA buffer and processed by the device through the automatic isolation and staining procedure.

#### CTC detection

The blood sample (5 ml) was diluted 1:2 with BD wash buffer (BD, USA) containing 0.2% paraformaldehyde (PFA), 0.1% bovine serum albumin (BSA), and 0.0372% EDTA. It was incubated for 10 min at room temperature and then detected by the device. The filtrate was gently aspirated by a vacuum suction pump. After aspiration, the retained cells were washed three times with pure water and fixed in 100% methanol. After disassembly from the filter, the membrane was placed on a slide and coverslipped after it had air-dried.

The slides were immersed in 100% xylene for several minutes at room temperature until the cover glasses dropped off. Then, we added eosin to the membrane for 2 min and then discarded it. Next, we added methylene blue for 1 min and then washed it with PBS. Then, the membrane was air-dried and observed by light microscopy (Qi et al., 2021; Zhu et al., 2022). The criteria for the identification of CTCs and CTC clusters used the cytomorphological criteria proposed by other research groups. The results of Wright’s staining were identified by two experienced cytopathologists.

#### MALBAC single-cell amplification

Before single-cell sequencing, we first use MALBAC single-cell amplification, and its experimental steps are as follows: (1) Isolation of the pre-amplification sample preparation area: Before amplification, the preparation process of pre-amplified samples needs to be completed in a separate isolated laboratory or dedicated work area, and special experimental materials and instruments are prepared; the DNA amplification product is stored separately from the pre-amplification reagent; (2) Control group DNA samples (5 μL) are prepared, including positive and negative controls; (3) Placing the cell lysate, pre-amplification enzyme, and amplification enzyme in an ice bath before use, and the other components should be thawed on ice before use; (4) Before the reaction, perform short centrifugation to ensure that the liquid in the reaction system is mixed evenly.

#### Single-cell sequencing

We use the Illumina platform for sequencing, its experimental steps are as follows:

(1) The oligonucleotide is a primer, and the library fragment is a template for DNA replication; (2) After the copy is completed, the library fragments are washed away, leaving the surface of the flow cell as DNA strands complementary to the library template; (3) Because the other end of the single-stranded DNA is a different joint sequence, it can bind to another adjacent oligonucleotide complementarily, followed by “bridge” amplification; (4) After 25–28 cycles are completed, the original single nucleotide sequence scattered on the surface becomes a scattered DNA cluster; (5) Dechain linearization again, cutting and washing the DNA strands on P5, leaving only the DNA strands on P; (6) Add the sequencing primer Read1 SP and the modified DNA polymerase to start DNA replication at the 3′ end of the sequencing primer; (7) To ensure the accuracy of sequencing, synchronous replication of each strand of a site DNA cluster is required; (8) Increase the sequencing length and perform sequencing in the other direction, that is, double-end sequencing.

### Model development preprocess

Each patient in the dataset had MR scans of four sequences: T1C, T1, T2, T2 flair, and tumor mask, along with classification labels.

The goal of this network is to segment three regions of glioma, including enhanced tumor area (ET), non-enhanced tumor area (NET), and edema area (ED); The tumor’s location, size, and classification information obtained from the target detection network were combined with the CTC numerical feature to differentiate the histological type and molecular type.

Four different experienced neurosurgeons, who also received guidance from a senior neuroradiologist (>10 years of clinical experience), applied Segmentation and Segment Editor modules to manually segment the original MRI dataset. All scans have been co-registered to the same anatomical reference using a rigid transform method on the 3D-slicer registration module. Skulls of the brain MRI were removed by 3D-slicer software that can eliminate the influence of skull areas with high-intensity signals. MR scans often display intensity non-uniformities due to variations in the magnetic field. Therefore, N4 bias field correction was used before the image input. We use data augmentation to increase the size of the dataset. To prevent over-fitting in training, data augmentation was used to expand the dataset.

The data augmentation methods used are as follows: (1) Adding random noise to the voxel, the noise worth ranged between −0.1 times and 0.1 times the standard deviation of the voxel. (2) Image size was changed to the original 0.9–0.1 times. (3) Random rotation and translation, with rotation ranging from −20 to +20°, and translation ranging from −30 to +30 and −15 to +15, respectively. (4) Random flip.

According to the 2021 WHO classification criteria, the molecular types of glioma were divided into 11 subcategories, and the histological type was divided into three grades. The grades, segmentations, and subcategories labels of each patient were one-hot encoded. In the preprocessing step, anchor boxes of the tumors were automatically generated according to the segmentation labels. The anchor box was the ground truth of the target detection task.

### Radiomic model development methods

The research of Choi et al. (2021) indicated that the location and shape characteristics of tumors have an important relationship with the IDH classification of gliomas. After adding six location numerical features, 13 shape numerical features, and one age numerical feature, the classification accuracy of IDH was improved by 1.6–5.3 percent compared with the traditional resnet classification model on the three different datasets (Choi et al., 2021). Inspired by that, we designed a model that fuses tumor localization features and shape features for classification. Compared with the radiomics method used in Choi’s et al. (2021) work to obtain tumor location and shape information, obtaining these features directly through the target detection network does not require additional manual operations, which is significantly more time-saving and convenient.

Our model consisted of a segmentation network, target detection network, and classification network. The outputs of the target detection network were first processed and then combined with the numerical information of the CTC to input the classification network to classify the images.

Our model structure was divided into four parts: backbone, the segmentation part, target detection part, and classification part. The model’s overall structure is shown in Figure 2. The target detection part was responsible for detecting the location, size, and classification information from the features which were extracted by the backbone. The part between the detection head and the backbone network was called the Neck, and the Neck part used the FPN which performed several upsampling after the end of the feature extraction section (Lin et al., 2017). The outputs of the upsampling layers were input into the detection heads to detect multiscale tumors. The position, size, and classification information of the detection box with the highest confidence were connected with the numerical features of the CTC to co-input a multi-layer perceptron (MLP) for classification. The upsampling part of the target detection network was extended until the feature map of the same size as the input image is obtained. In this process, the high-resolution feature map from the feature extraction part is also received to fuse the high-resolution information and the high-semantic information to form the segmentation part. The structure of the overall segmentation part is similar to the commonly used medical image segmentation network UNet (Ronneberger et al., 2015).

**Figure 2 fig2:**
[figure not shown]
The “integrated diagnosis” model structure. The model is composed of four parts. Features are extracted by backbone first, in the up-sampling process, the object detection part is responsible for extracting the bounding box and classification features, and the segmentation part is responsible for segmenting the tumor region. The output of target detection is connected with the CTC numerical feature as the input of MLP for classification.

### Backbone

We choose a tiny Cross Stage Partial Network (CSPDarkNet-tiny) as the backbone of the network, which is used to extract useful features in the input images, and the structure of the backbone is shown in Figure 3. The CSPDarkNet-tiny was improved from the DarkNet53-tiny network, inspired by the work of CSPNet (Wang et al., 2020). CSPNet solves the problem of large computation in inference from the perspective of network structure design. The feature extraction part mainly used two kinds of layers: 3-dimensional Convolution + Instance Normalization + Leaky ReLU (CIL) and residual block (Ulyanov et al., 2016). The batch size in our experiment is usually only 1–2, and using batch normalization will lead to model instability (Ioffe and Szegedy, 2015), so instance normalization was used in our network (Wu and He, 2018). The feature extraction section completed 32 x downsampling to facilitate adequate feature extraction. Moreover, the number of convolution convolutions in each stage of the feature extraction part is different, and each residual block contains three convolution operations, mainly because some studies indicate that the model performs better when the deep network blocks (convolution + normalization + activation) have much number of layers (He et al., 2016; Woo et al., 2018; Liu et al., 2022).

**Figure 3 fig3:**
[figure not shown]
Backbone structure. CSPDarkNet-tiny is used as the backbone for feature extraction, connecting the upper sampling part through the attention mechanism at the first and third layer from the last.

### Segmentation part

The segmentation network was formed by extending the upsampled part of object detection until the obtained feature map has the same size as the input feature. The overall network structure was U-shaped, and the segmentation head divided the tumor into four regions: ET, NET, ED, and background.

### Target detection part

Adjacent feature maps from the bottom-up and top-down were concatenated together on the channel and then input to the detection head. Therefore, the input of the head contained rich spatial information from the bottom-up and rich semantic information from the top down. As shown in Figure 3, the Neck part mainly adopts the FPN structure. In addition, to better integrate the features from the backbone network, we also used the CBAM module, whose specific structure is shown in Figure 4. The output of the head contains a lot of bounding boxes with confidence features, position features, size features, and classification features of the bounding boxes. The confidence represents the Intersection over Union (IOU) between the prediction box and the ground truth box. The features of the prediction box with the largest confidence were extracted as the input of the classification network.

**Figure 4 fig4:**
[figure not shown]
CBAM module. **(A)** CBAM module is consist of channel attention module and spatial attention module. **(B)** The structure of channel attention module and spatial attention module.

### Classification part

The features from the target detection network contained 14 classification features (WHO 3, molecular type 11) and 6 box features (location 3, size 3). The location and size of the prediction box represented the location and size of the glioma to some extent. These numerical features were combined with CTC numerical features and then input into the MLP module which is shown in Figure 5. The outputs of MLP were input into the softmax layer to obtain the final classification of WHO grades and molecular subtypes.

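### Age is collected and was in the feature set of the study behind the design, but the classifier omits it without a reason; if CTC tracks age, a gain from CTC could partly reflect age

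*Protocol article*

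**What the plan says.** - **Age is available.** Protocol article, Data collection: "We will collect baseline characteristics from glioma patients, including age, sex, preoperative MRI datasets". Participant criterion also sets a lower age limit.
- **The evidence behind the design included age.** Radiomic model development methods cites an earlier study: "After adding six location numerical features, 13 shape numerical features, and one age numerical feature", it reports, "the classification accuracy of IDH was improved by 1.6–5.3 percent compared with the traditional resnet classification model".
- **The trial takes over part of it.** The same paragraph continues: "we designed a model that fuses tumor localization features and shape features for classification". Age is not mentioned again as a model input.
- **The classifier inputs are listed.** Classification part counts "14 classification features (WHO 3, molecular type 11) and 6 box features (location 3, size 3" and then says "These numerical features were combined with CTC numerical features and then input into the MLP module". The Figure 2 caption agrees: "The output of target detection is connected with the CTC numerical feature as the input of MLP for classification".
- **The hypothesis concerned.** The last paragraph of Related study hypothesises that adding CTC to the multi-task model improves integrated diagnostic performance.

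**The concern.** The second aim of the study is about incremental value: whether a blood test adds to what imaging already tells the clinician. An increment depends on what is in the comparator. Age costs nothing and is known before surgery, so it belongs among what the clinician already has. If neither model contains age, comparing them with and without CTC cannot separate information specific to CTC from any age information that CTC carries.

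The article's background does not settle this. Related study and Discussion report that CTC is related to IDH status and do not mention age. Discussion adds that the relation of CTC to the other important molecular targets has not been explored further.

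Two things are at stake: some accuracy that age might have supplied, and the interpretation of any CTC gain.

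**Working it through.** **1. Count the inputs.**
- Cited study: 6 location + 13 shape + 1 age = 20 added features.
- This trial: 14 classification + 6 box = 20 features, plus CTC. None is age. The text of Radiomic model development methods and of Classification part agrees with the Figure 2 caption.

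**2. Ask what the cited gain says about age.** The 1.6–5.3 percent gain is for all 20 added features together, for IDH only, against another model. It cannot be split, so no part of it measures age.

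**3. Look for a size in the article.** There is none: no age–marker effect, no age–CTC correlation and no expected CTC increment. The 0.10 under Sample size is a single AUC of 0.80 against a null of 0.70, not a gain from CTC. Any magnitude is therefore an illustration.

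**4. Illustration, binormal scores.** Assumptions: imaging AUC 0.80; age AUC 0.70 for some marker; CTC carries no information beyond age. Let r be the age–CTC correlation and ρ the age–imaging correlation, both within marker class and with scores oriented towards the marker.

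Formulas: d = √2 × Φ⁻¹(AUC). For two scores with correlation c, D² = (d₁² + d₂² − 2c·d₁·d₂)/(1 − c²), and the combined AUC is Φ(D/√2). Here d for imaging is 1.190 and d for age is 0.742. For CTC, d = r × 0.742 and c = r × ρ.

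*Benefit of age itself.* At ρ = 0, D² = 1.417 + 0.550 = 1.967, so D = 1.402 and AUC = 0.839. At ρ = 0.3 the AUC is 0.813, and at ρ = 0.5 it is 0.802. With age AUC 0.65 or 0.75 and ρ = 0, it is 0.823 or 0.860.

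*Spurious CTC gain, worked cases.*
- r = 0.5, ρ = 0: d for CTC = 0.371; D² = 1.417 + 0.138 = 1.554; AUC 0.811; gain 0.011.
- r = 0.8, ρ = 0: d for CTC = 0.593; D² = 1.417 + 0.352 = 1.769; AUC 0.826; gain 0.026.
- r = 0.5, ρ = 0.5: c = 0.25; D² = (1.554 − 0.221)/0.9375 = 1.422; AUC 0.8005; gain 0.0005.
- r = 0.8, ρ = 0.5: c = 0.40; D² = (1.769 − 0.565)/0.84 = 1.433; AUC 0.801; gain 0.001.

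| Age–CTC correlation r | ρ = 0 | ρ = 0.3 | ρ = 0.5 |
|---|---|---|---|
| 0 | 0 | 0 | 0 |
| 0.3 | 0.004 | 0.001 | 0.000 |
| 0.5 | 0.011 | 0.003 | 0.0005 |
| 0.8 | 0.026 | 0.008 | 0.001 |

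The gain nearly vanishes at ρ = 0.5 because age then tells the classifier little that the imaging score does not. A negative ρ would enlarge it.

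**5. Cross-check by simulation.** Logistic models on 200,000 simulated records, with marker prevalence 40%, imaging AUC 0.70, age independent of imaging, and age effects of 0.5, 0.8 and 1.2 SD. Adding age raises the AUC to about 0.74, 0.78 and 0.84. A CTC with no information of its own shows a gain of 0.000 at r = 0, 0.003 to 0.015 at r = 0.3, and 0.010 to 0.041 at r = 0.5. With age in the comparator the gain is 0.000 in every case.

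**The case against.** Using part of a cited design is a legitimate modelling choice. The article says which part it adopts, and explains that a detection network obtains location and shape without manual work. No passage reports an age–CTC association, and without one there is no proxy effect. The larger figures need a moderate to strong age–CTC correlation and independence of age from imaging, neither of which the article supports. An article is also condensed, so an age-adjusted comparison could stand in a fuller document.

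Much of this stands. A reader might infer that the omission costs accuracy, because the cited study gained 1.6–5.3 percent. The article does not support that, since the gain is joint over 20 features and for IDH only. A reader might also infer that any CTC gain would be age in disguise. That is not supported either: it is a possibility that depends on an association nobody has reported here. Nor does the article contradict itself in adopting location and shape alone.

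The point about condensing does not remove the concern. The classifier inputs are stated and counted, so the omission of age is a positive feature of the described model. The reason given for using a detection network explains how location and shape are obtained; it does not explain why age, which needs no extraction, is left out.

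**Conclusion.** The point holds in a limited form. Age is collected, it belonged to the feature set of the study that inspired the design, and the stated inputs leave it out without a reason. The model forgoes a predictor that may help, and its CTC comparison stays open to age as an alternative explanation, provided CTC and age are associated.

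No effect size can be derived from the article. Under the assumptions in the working, the spurious gain runs from nothing to 0.026 in AUC for the binormal case, and up to 0.041 in the simulation with the strongest age effect. It shrinks towards zero under a moderate positive age–imaging correlation. Confidence that age is omitted is high; confidence in the size of the consequence is low to moderate. The change is worth making because it removes the ambiguity whatever the true correlations are.

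**What to change.** In the two hospital cohorts, where age and CTC are collected, add age to the MLP inputs of both the radiomics-only and the radiomics-plus-CTC models. Judge CTC by its gain over the model that includes age. State this in Radiomic model development methods (where the model structure is set out) and in Classification part. If age is left out deliberately, give the reason there. Sex is also collected and could be added, but this is optional: nothing in the article supports it as a predictor.

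Cost: one more numeric input to a small network. Learning curve during the process of model training describes the classification part as trained in a separate second stage, so the detection and segmentation networks need no redesign. The hospital cohorts need no new data item. Records from the public dataset may lack age, which is why the comparison is best confined to the hospital cohorts. The CTC gain may turn out smaller.

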**Figure 5 fig5:**
[figure not shown]
Classification module. Non-invasive prediction of Histology type and Molecular type of gliomas.

### Loss function

The loss function consists of four parts: coordinate loss, confidence loss, classification loss, and segmentation loss. The confidence loss and regression loss in the object detection part refer to the YOLOv4 model (Bochkovskiy et al., 2020). Cross entropy loss was used as classification loss and segmentation loss.

#### Coordinate loss

$$L_{coord}=\lambda_{\mathrm{coord}}\sum_{i=0}^{H\times W\times D}\sum_{j=0}^{M}I_{ij}^{obj}\left(2-w_{i}\times h_{i}\right)\left(1-DIOU\right)$$

$\lambda_{\mathrm{coord}}$
 represents the weight coefficient of coordinate loss, 
$\sum_{i=0}^{H\times W\times D}\sum_{j=0}^{M}$
 indicates traversing all prediction boxes, 
H,W
, and 
D
 are the sizes of feature maps, 
M
 is the number of anchor boxes at each grid cell on the feature map, 
$I_{ij}^{obj}\;$
represents whether it is a positive sample (the IOU of the prediction box and ground truth box is >0.5 and is the largest), which is either 0 or 1. The specific expression of 
DIOU
is shown in Equation (2):

$$\begin{array}{c} \mathrm{DIoU}=\mathrm{IoU}-\frac{\rho^{2}\left({\mathrm{b,b}}^{\mathrm{gt}}\right)}{c^{2}} \end{array}$$

Where,
$\;\rho^{2}\left(b,b^{gt}\right)$
 represents the Euclidean distance between the center points of the prediction box and the ground truth box, and c represents the Euclidean distance that can contain the center points of both the prediction box and the ground truth box (Zheng et al., 2019).

#### Confidence loss

$$\begin{array}{c} L_{\mathrm{conf}}=\lambda_{\mathrm{conf}}\left[-\sum_{i=0}^{K\times K}\sum_{j=0}^{M}I_{\mathrm{ij}}^{\mathrm{obj}}\log\left(C_{i}\right)-\sum_{i=0}^{K\times K}\sum_{j=0}^{M}I_{\mathrm{ij}}^{\mathrm{noobj}}\log\left(1-C_{i}\right)\right] \end{array}$$

The two terms equation refer to positive sample confidence loss and negative sample confidence loss, respectively. 
$I_{\mathrm{ij}}^{\mathrm{noobj}}$
 represents the negative sample, whose IOU of the prediction box and label box is <0.1.
$\;\;\lambda_{\mathrm{conf}}$
 represents the weight coefficient of confidence loss.

